### Who will take informed consent? {26a}

#### Additional consent provisions for collection and use of participant data and biological specimens {26b}

A key tenet of this study is that clinical care is a clinical decision with children receiving care in accordance with the pathway allocated to the site. However, prior to collecting any patient data or biospecimens, informed consent is required along with assent as appropriate. To enable this approach, once a child is identified as being pathway eligible, a member of the clinical care team will provide patients/caregivers with an information sheet (Appendix). This document states that the site is participating in a study and it includes information regarding the institution’s allocated pathway, that there is no accepted standard of care, and the pros and cons of the two treatment pathways. Patients/caregivers will discuss whether to follow the allocated pathway and the alternate options with their responsible physician. Regardless of the clinical decision made, the research team will be alerted to the potentially eligible participant and they will reach out to the responsible physician and request permission to contact the family. If obtained, a member of the research team will approach the family to obtain research consent (Fig. 2) to permit data and biospecimen collection along with consent for the conduct of future studies with the biospecimens and to re-contact the participant for future ancillary studies.

**Fig. 2 Fig2:**
[figure not shown]
Illustration of the participant flow through the study. Clinical decision point: patients and caregivers are presented with the standard medical risks associated with STEC infection, the known pros/cons of available treatment options, and the treatment currently recommended due to the study allocation. Research decision point: patients and caregivers can consent to data and biospecimen collection

## Interventions

### Explanation for the choice of comparators {6b}

Both treatment pathways reflect widely accepted, albeit usually implemented in a non-standardized manner, treatment approaches used in North American Institutions. As it is unknown which approach is most beneficial, there is equipoise. Both pathways have been reviewed and accepted by critical stakeholders at each institution (including emergency medicine, nephrology, gastroenterology, infectious diseases and hospital medicine) as reasonable and appropriate care options. Embedding protocolized management of either clinical approach (i.e., hyperhydration or conservative fluid management) may lead to improvements over current practice, reducing undesirable outcomes by avoiding dehydration, use of antibiotics or antimotility-agents, and by facilitating close follow up and early recognition of complications.

### Intervention description {11a}

#### Fluid protocol #1—hyperhydration

In this pathway, all eligible children are admitted for the administration of intravenous fluids. To rapidly and safely achieve intravascular volume expansion, based on existing evidence [19, 20, 28], the starting intravenous fluid volume will be 200% of maintenance fluids calculated using the Holliday–Segar formula [38] with the rate adjusted based on clinical parameters and targets.

The following specifics will form the basis of the fluid management protocol (Fig. 3):

**Fig. 3 Fig3:**
[figure not shown]
The hyperhydration care pathway recommends the infusion of 200% maintenance fluids until a hematocrit reduction of 20% and weight gain of 10% occur. Patients may be discharged if the following criteria are met even if the targets are not achieved: (1) platelet count is > 50 × 10^9^/L (in absence of transfusion) AND they have increased by ≥ 5%* since the preceding test AND (2) absence of diarrhea (loose or watery stool) × 24 h AND (3) ≥ 5 days since the onset of diarrhea. *If > 10 days since the onset of diarrhea, up to a 5% decrease in platelet count since preceding test is acceptable

Reversal of dehydration: initial rehydration strategies should focus on rapidly reversing dehydration.Infusion of 200% of maintenance fluids × 24 h provided, ideally, as a balanced crystalloid (e.g., PlasmaLyte™, Ringer’s Lactate) intravenous solution. Electrolytes and dextrose may be administered as deemed appropriate; customized solutions are permitted. Intravenous fluid solutions containing < 130 mEq/L sodium should be avoided as they increase the likelihood of developing hyponatremia and are less effective in achieving intravascular volume expansion.If the hematocrit reduction is < 20% from the initial value at 24 h, and the weight gain is < 10%, repeat step #2 (infusion of 200% maintenance intravenous fluids for 24 additional hours) unless the weight gain is ≥ 10% in which case move to step #5.Oral fluids permitted ad lib.If the target hematocrit reduction (20% decrease from baseline) AND a 10% weight gain are achieved, adjust total intravenous fluid volume to maintain targeted weight gain and prevent worsening fluid accumulation (i.e., replace insensible losses plus urine and stool output). If both targets are not achieved, then return to step #2.◦ Insensible losses will be estimated to be 400 mL/m^2^ and these losses should be replaced, along with additional losses through output, every 4 to 6 h [39].◦ Daily weights should be performed and be used to guide the assessment of fluid status with additional fluid adjustments made, as required, to maintain the targeted weight gain.Complete blood count, electrolytes, and kidney function should be repeated every 24 h (or more frequently as deemed clinically indicated).Consider nephrology consultation for all children.

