#### Safety targets

Based on the use of this fluid protocol in children with HUS who experienced a mean weight gain of 12.5% without any serious adverse events (SAEs) [18], we have identified parameters ((1) weight gain of 10% AND (2) evidence of hemodilution (i.e., 20% reduction in hematocrit)) which will serve to indicate that intravascular volume expansion has been achieved. This dual parameter approach ensures that hemodilution does not simply reflect hemolysis due to the ongoing microangiopathic process while also identifying a maximal weight gain target to help limit the risk of volume overload.

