### Criteria for discontinuing or modifying allocated interventions {11b}

Treatment decisions will be at the discretion of the responsible physician who may choose to deviate from to the allocated pathway. Clinical events and participant preference may lead to care modifications; these would not affect the conduct of study activities (e.g., follow-up). Specific documentation will be made regarding allocated pathway adherence, participant withdrawal, and study discontinuation.

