### Strategies to improve adherence to interventions {11c}

Site investigators and champions at each site, which include a pediatric emergency medicine physician, nephrologist, pediatric hospital medicine specialist, and at certain sites a gastroenterologist, and/or infectious disease specialist, will be responsible for educating all relevant individuals (at the participating site and in their catchment/referral area) including attending physicians and trainees regarding the treatment pathways. All pathway eligible children will be monitored in real-time, and support will be provided to the clinical care team regarding pathway adherence which has been facilitated through the building and implementation of clinical care order sets embedded into the electronic medical record (EMR) at participating sites.

For each patient, the EMS (emergency medical services) Data Center (EDC, Salt Lake City, UT) will classify the amount of fluid administered in relation to their target as defined by the pathway to which the site has been allocated. Adherence at an individual patient level will be reviewed during weekly leadership team meetings and those cases where participants met our study definition of non-adherence (> 110% and < 175% maintenance fluids in the conservative fluid management and hyperhydration groups, respectively) will undergo review to identify potential etiologies and solutions in an attempt to mitigate future such events.

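### The hyperhydration steps give conflicting directions for a child who has gained 10% in weight but whose hematocrit has fallen by less than 20%

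*Protocol article*

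**What the plan says.** All of this is in the current text of the Protocol article. The list numbers in Fluid protocol #1 (hyperhydration) are lost in the extracted text, but the order and the cross-references identify the steps.

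- **Step 2**: 200% of maintenance for 24 h.
- **Step 3**: at 24 h, if the hematocrit fall is under 20% and the weight gain under 10%, repeat step 2. There is an exception for weight gain of 10% or more, "in which case move to step #5".
- **Step 5**: if the hematocrit target AND (capitalised in the text) the 10% weight gain are reached, hold the weight by giving insensible losses plus output: "these losses should be replaced, along with additional losses through output". Then: "If both targets are not achieved, then return to step #2".
- **Fig. 3 caption**: "infusion of 200% maintenance fluids until a hematocrit reduction of 20% and weight gain of 10% occur".
- **Safety targets**: both parameters together define achieved expansion. The pair is also described as "identifying a maximal weight gain target to help limit the risk of volume overload". The section reports earlier use of this fluid protocol in "children with HUS who experienced a mean weight gain of 12.5% without any serious adverse events".
- **End-of-fluid protocol criteria**: weight gain above 15% ends the pathway.
- **Criteria for discontinuing or modifying allocated interventions**: treatment is "at the discretion of the responsible physician who may choose to deviate".
- **Adherence, hyperhydration**: the window closes when any termination criterion is met, with weight/hematocrit targets given as one example, or at 48 h if that is sooner. Whether one target or both is needed is not said. The data center "will classify the amount of fluid administered in relation to their target as defined by the pathway".

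**The concern.** This is the dosing rule of the experimental arm, and it is built into order sets at the sites. If it can be followed in two ways, sites may deliver two different treatments to the same kind of child. On one reading, 200% fluids continue past the weight gain that the protocol describes as a ceiling against overload.

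The > 15% stop does not say what to do between 10% and 15%. Scheduled weights are daily, so a child could cross that band between two weighings. Low output is plausible in this population. Entry excludes absent urine output for more than 24 h, and the pathway stops at 12 h of anuria, but oliguria alone triggers neither.

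There is a smaller, conditional issue in scoring adherence, because the end of the window depends on the same unresolved question.

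**Working it through.** **1. Trace of the four states at the 24 h check**

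| Hematocrit fall | Weight gain | Step 3 | Step 5 | Fig. 3 caption |
|---|---|---|---|---|
| < 20% | < 10% | repeat 200% | return to 200% | 200% |
| ≥ 20% | ≥ 10% | does not call for a repeat | replace losses | 200% ends |
| ≥ 20% | < 10% | silent | return to 200% | 200% |
| < 20% | ≥ 10% | do not repeat; go to step 5 | return to 200% (not both met) | 200% |

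Only the last row conflicts. If step 5's fallback means that neither target is met, step 5 gives this child no instruction, and the caption still contradicts step 3.

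**2. Illustrative size of the 10–15% band**

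Inputs from the article: 200% of Holliday–Segar maintenance, insensible loss of 400 mL/m2, stop above 15%. Assumptions of this review: standard Holliday–Segar coefficients (1000, 1500, 1900 and 2500 mL/day at 10, 20, 40 and 70 kg); body surface 0.5, 0.8, 1.3 and 1.8 m2; insensible loss taken as per day; 1 L counted as 1 kg; oral intake not counted; rate not adjusted within the 24 h.

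Output needed to stay at or below +15%, starting from +10%: (200% volume − insensible loss − 5% of body weight) / (kg × 24).

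- 10 kg: 2000 − 200 − 500 = 1300 mL, or 5.4 mL/kg/h
- 20 kg: 3000 − 320 − 1000 = 1680 mL, or 3.5 mL/kg/h
- 40 kg: 3800 − 520 − 2000 = 1280 mL, or 1.3 mL/kg/h
- 70 kg: 5000 − 720 − 3500 = 780 mL, or 0.5 mL/kg/h

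Further gain over 24 h at 20 kg, by urine plus stool output:

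- 1 mL/kg/h: 3000 − 320 − 480 = 2200 mL, or 11.0%
- 2 mL/kg/h: 3000 − 320 − 960 = 1720 mL, or 8.6%
- 4 mL/kg/h: 3000 − 320 − 1920 = 760 mL, or 3.8%

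Replacement under step 5 would instead hold the weight steady.

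Can the first 24 h of infusion alone bring a child to +10%? At 10 kg, 2000 mL against 1000 mL, and at 20 kg, 3000 against 2000: possible, depending on losses. At 40 kg, 3800 against 4000, and at 70 kg, 5000 against 7000: not possible even with no losses. The illustration therefore matters mainly for smaller children.

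**3. Adherence score (threshold 175% of maintenance)**

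- Fluids cut on weight at 24 h, window ends on weight: 200 × 24 / 24 = 200%, adherent.
- Fluids continued until both targets are met, window 48 h: 200 × 48 / 48 = 200%, adherent.
- Fluids cut to 100% on weight at 24 h, but scored over 48 h: (200 × 24 + 100 × 24) / 48 = 150%, nonadherent. Any replacement rate below 150% has this effect, since (200 + 150) / 2 = 175.

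**The case against.** The strongest counter-reading treats step 3 as routing only. Any child at 10% or more goes to step 5, where the two-target test is applied. The capitalised AND, the caption and the dual-parameter definition under Safety targets then agree, bounded by the 15% stop. Step 3 never says in words that 200% must stop, and its condition already requires weight gain under 10%, so its exception is awkward on any parsing. Fig. 3 itself is not shown, and the working order sets may be clearer.

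Part of this stands: the intended rule is uncertain. It does not remove the conflict. On the routing reading, step 3's exception does nothing for the child at issue, who is sent to step 5 only to be returned to the infusion just excepted, and a maximal weight target still sits badly with continuing 200%.

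The fluid-balance figures also deserve caution. The Intervention description says the rate is adjusted on clinical parameters and targets, whereas the calculation holds it fixed.

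A reader might infer that the pathway is shown to be unsafe, or that weight alone was plainly meant to govern. The documents support neither: a mean gain of 12.5% without serious adverse events is reported, and the text backs both rules.

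**Conclusion.** The point holds as a conflict in a stated dosing rule. For weight gain of at least 10% with a hematocrit fall under 20%, step 3 points away from a further 200% infusion, while step 5 (on its natural reading) and the caption point back to it. Between 10% and 15%, the only bounds are the > 15% stop, daily weights, rate adjustment and the physician's freedom to deviate. It should be fixed.

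The number of children who reach this state is unknown. The volumes above are illustrations that rest on the listed assumptions.

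A reader might also infer that the per-protocol set is compromised. That follows only if fluids are cut on weight alone and then scored on a both-targets window. No section states that combination, and ending the window at any criterion, whichever comes first, argues against it. The intention-to-treat analysis set is unaffected.

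**What to change.** State one rule for this state and use it identically in step 3, step 5, the Fig. 3 caption, the order sets and the end of the adherence window.

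- **Rule that fits step 3 and the stated overload purpose**: once weight gain is 10% or more, reduce to replacing insensible, urine and stool losses even if the hematocrit target is unmet. Return to step 2 only while weight gain is below 10%. Keep > 15% as the hard stop and close the adherence window at the same 10% point. The downside is less volume expansion for children whose hematocrit target is unmet; hematocrit becomes a monitored marker and no longer gates the reduction.
- **If both targets are meant to be required**: delete step 3's exception and the word maximal, and set out explicitly the 10–15% range and how it is monitored.

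This is the sponsor's choice; the text does not settle it. Either option costs a protocol clarification, an order-set check and one line in the adherence definition. Recruitment began in September 2022, so the effective date should be recorded in case sites have already followed different readings.

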#### Safety targets

Based on the use of this fluid protocol in children with HUS who experienced a mean weight gain of 12.5% without any serious adverse events (SAEs) [18], we have identified parameters ((1) weight gain of 10% AND (2) evidence of hemodilution (i.e., 20% reduction in hematocrit)) which will serve to indicate that intravascular volume expansion has been achieved. This dual parameter approach ensures that hemodilution does not simply reflect hemolysis due to the ongoing microangiopathic process while also identifying a maximal weight gain target to help limit the risk of volume overload.

#### Fluid protocol #2—conservative fluid management

The conservative fluid protocol has been designed to align and integrate into existing practice patterns. Clinicians can manage children as they normally would with a target of euvolemia. In this pathway, children will undergo a protocolized baseline evaluation that includes reversal of dehydration, if present, and close laboratory monitoring (Fig. 4). The need and approach to reverse dehydration, if present, is at the discretion of the clinical care team. In the absence of evidence of microangiopathy (i.e., normal urinalysis, lactate dehydrogenase, hemoglobin and platelet counts, and creatinine concentrations), the decision to admit or discharge the child is at the discretion of the clinical care team. If microangiopathy is present, admission for monitoring is recommended.

**Fig. 4 Fig4:**
[figure not shown]
The conservative fluid management pathway leaves the decision to admit the child to the discretion of the clinical care team. If microangiopathy is present admission is encouraged. For inpatients and outpatients, laboratory monitoring should be performed a minimum of every 24 h until discharge criteria are met. If intravenous fluids are administered, the maximum rate is 100% of maintenance and the target is euvolemia and maintaining weight gain below < 5%. The pathway should be discontinued once the same criteria are achieved as for the hyperhydration pathway (Fig. 3)

#### The hospitalization protocol includes

Reversal of dehydration: initial rehydration strategies should focus on rapidly reversing dehydration.Targeting euvolemia: intravenous fluids should be administered at a maximum rate of 100% maintenance with the rate adjusted to take into consideration ongoing losses (e.g., vomiting, diarrhea, third spacing) and oral fluid intake.◦ The intravenous fluid administered should be isotonic with the volume calculated employing the Holliday–Segar formula [38] with adjustments made as needed to target euvolemia.◦ The fluids provided should be balanced crystalloid (e.g., PlasmaLyte™, Ringer’s lactate) with electrolytes and dextrose added as deemed appropriate; customized solutions are permitted. Intravenous fluid solutions containing < 130 mEq/L sodium should be avoided as they increase the likelihood of developing hyponatremia.Monitoring◦ Daily weights should be performed and be used to guide the assessment of fluid status with additional fluid adjustments made, as required, to maintain euvolemia and weight gain < 5% above baseline.◦ Complete blood count, electrolytes, and kidney function should be repeated every 24 h.Consider nephrology consultation for all children.

#### The outpatient management protocol includes

Reversal of dehydration: initial rehydration strategies should focus on rapidly reversing dehydration, if present.Targeting euvolemia: oral fluids permitted ad lib.◦◦ Encourage oral fluid intake as per routine gastroenteritis dehydration management approaches.Monitoring:◦ Complete blood count, electrolytes, and kidney function should be repeated every 24 h.◦ Emergency department evaluation required if laboratory tests or clinical symptoms concerning for HUS. These include any of the following:◾ New bleeding, bruising, petechial rash◾ Severe abdominal pain◾ Unusual/severe headache◾ Tea-colored urine◾ No urine output for 12 h◾ Irritability/ altered mental status◾ EdemaOutpatient management otherwise as per the clinical care team.

#### Goal

Once dehydration has been reversed, fluid targets should aim to maintain euvolemia and avoid dehydration.

### Criteria for discontinuing or modifying allocated interventions {11b}

Treatment decisions will be at the discretion of the responsible physician who may choose to deviate from to the allocated pathway. Clinical events and participant preference may lead to care modifications; these would not affect the conduct of study activities (e.g., follow-up). Specific documentation will be made regarding allocated pathway adherence, participant withdrawal, and study discontinuation.

#### End-of-fluid protocol criteria

The pathways will end when the at-risk window for developing HUS, or worsening HUS if present, has passed and this time point is defined by:Platelet count is > 50 × 10^9^/L (in the absence of transfusion) ANDPlatelets have increased by ≥ 5%* (in the absence of transfusion) since preceding test ANDAbsence of diarrhea (loose or watery stool) × 24 h AND ≥ 5 days since the onset of diarrhea

*If >10 days since the onset of diarrhea, up to a 5% decrease in platelet count since preceding test is acceptable.

In addition, the fluid pathways should no longer be followed in children meeting any of the following criteria:Decision to initiate RRTAnuria for ≥ 12 hHypoxemia requiring supplemental oxygenWeight gain > 15%Hypertensive emergency

If *any of* these criteria are met, the treatment pathway will not resume once they are resolved; care tailored to each patient should be provided as directed by the responsible physician.

### Strategies to improve adherence to interventions {11c}

Site investigators and champions at each site, which include a pediatric emergency medicine physician, nephrologist, pediatric hospital medicine specialist, and at certain sites a gastroenterologist, and/or infectious disease specialist, will be responsible for educating all relevant individuals (at the participating site and in their catchment/referral area) including attending physicians and trainees regarding the treatment pathways. All pathway eligible children will be monitored in real-time, and support will be provided to the clinical care team regarding pathway adherence which has been facilitated through the building and implementation of clinical care order sets embedded into the electronic medical record (EMR) at participating sites.

For each patient, the EMS (emergency medical services) Data Center (EDC, Salt Lake City, UT) will classify the amount of fluid administered in relation to their target as defined by the pathway to which the site has been allocated. Adherence at an individual patient level will be reviewed during weekly leadership team meetings and those cases where participants met our study definition of non-adherence (> 110% and < 175% maintenance fluids in the conservative fluid management and hyperhydration groups, respectively) will undergo review to identify potential etiologies and solutions in an attempt to mitigate future such events.

### Hyperhydration

Data related to all intravenous fluids administered will be extracted from the medical record. For the calculation of pathway adherence, the intravenous fluid administration period begins (i.e., time of study initiation) at the:Time of hospital admission plus 2 h (for participants asked to come to the hospital)* ORTime the participant met eligibility criteria plus 2 h (for participants already in hospital)* ORActual time of initiation of intravenous fluid administration if occurs before the additional 2-h period has lapsed

*Some participants will be admitted into the hospital before eligibility, and some will become eligible before admission (i.e., positive STEC result in child who is at home). The later of the time points between options (1) and (2) will be used to determine the timing of study initiation if (3) does not apply.

The intravenous fluid administration period ends (i.e., time of study end for pathway adherence determination) when any fluid protocol termination criteria are met (i.e., weight/hematocrit targets, complication ensues, end-of fluid protocol criteria) or after 48 h of fluid administration—whichever happens first. The targeted volume of fluid is defined by the administration of ≥ 175% of maintenance fluids calculated according to the Holliday–Segar formula for the duration of time the participant was in the volume expansion phase of the protocol [38]. Thus, adherence is defined as the administration of fluids in excess of: 100% maintenance fluids × 1.75 × number of hours the participant was in the volume expansion phase of the protocol. Boluses will be included in the quantification of total fluids. Exact monitoring and recording of oral fluid intake are logistically prohibitive and will not be included in the fluid calculation.

The management of patients who receive < 175% of maintenance intravenous fluids in the hyperhydration arm will be classified as nonadherent. However, all patients will be included in the intent-to-treat (ITT) analyses regardless of the volume of fluids administered; secondary analyses will include a per protocol adherence analysis.

